# Data visualization as an intervention for pediatric chronic pain: a pilot feasibility study protocol for a randomized controlled crossover trial

**DOI:** 10.1186/s40814-022-01170-5

**Published:** 2022-10-03

**Keywords:** Chronic pain, Children and adolescents, Data visualization

## Abstract

**Background:**

Chronic pain is a common and costly condition in youth, associated with negative implications that reach far beyond the pain experience itself (e.g., interference with recreational, social, and academic activities, mental health sequelae). As a self-appraised condition, pain experience is influenced by patient’s biases and meaning-making in relation to their symptoms and triggers. We propose that interacting with self-reported data will impact the experience of pain by altering understanding and expectations of symptom experience and how pain interacts with other factors (e.g., sleep, emotions, social interactions). In this study, we aim to establish the feasibility and acceptability of using a data visualization platform to track and monitor symptoms and their relationship with other factors, versus simply daily reporting of symptoms using a smartphone-based Ecological Momentary Assessment (EMA).

**Methods:**

This protocol is for a randomized, single-center, open-label crossover trial. We aim to recruit 50 typically developing youth aged 12–18 years with chronic pain to take part in two phases of data collection. The trial will utilize an A-B counterbalanced design in which participants will be randomly assigned to receive either Part A (EMA alone for 7 days) or Part B (EMA plus visualization platform for 7 days) first and then receive the opposite phase after a 7-day break (washout period). Key outcomes will be participant reports of acceptability and feasibility, EMA completion rates, barriers, and perceptions of the benefits or risks of participation. Secondary exploratory analyses will examine the relationship between EMA-reported symptoms over time and in relation to baseline measures, as well as pilot data on any improvements in symptoms related to engaging with the data visualization platform.

**Discussion:**

This protocol describes the feasibility and pilot testing of a novel approach to promoting self-management and facilitating symptom appraisal using visualized data. We aim to determine whether there is a sufficient rationale, both from the perspective of feasibility and patient satisfaction/acceptability, to conduct a larger randomized controlled trial of this intervention. This intervention has the potential to support clinical care for youth with chronic pain and other conditions where self-appraisal and understanding of symptom patterns are a critical component of functional recovery.

**Trial registration:**

Open Science Framework doi: 10.17605/OSF.IO/HQX7C. Registered on October 25, 2021, osf.io/hqx7c

**Supplementary Information:**

The online version contains supplementary material available at 10.1186/s40814-022-01170-5.

## Introduction

### Background and rationale

Chronic pain is a common, costly condition in youth, of whom 3–5% report disabling levels of chronic pain [1]. Even more youth (20–30%) report recurrent pain that is not disabling, but still interferes with academic, social, and recreational functioning, and that has significant effects on mental health (e.g., higher rates of anxiety, depression, and post-traumatic stress symptoms) and quality of life [2–5]. As a self-appraised condition, pain is whatever the patient says it is. Self-appraisals can be biased by our attention, interpretations, and memory. We posit that interacting with lived-experience data—through viewing and reflecting on daily patterns—will help patients understand and communicate their pain experience and the factors that influence it, enabling a process of active engagement leading to pain relief, thereby making “the data the drug”.

Ecological momentary assessment (EMA) is used to obtain in-the-moment longitudinal assessments of feelings or behavior in the context of daily social life [6, 7] and enhance psychological interventions [8, 9]. EMA methodology has been frequently used in adult chronic pain research [10], but has been underused in pediatrics. To date, the majority of the literature on the use of EMA (or similar methods, such as daily diaries) in pediatric chronic pain has focused on specific disease populations (e.g., sickle cell disease, cancer, arthritis, headache) and the EMA has primarily measured features of the pain (e.g., intensity, location), sleep, functioning, and medication use [11–17]. EMA can be used to quantify changes in anxiety over time [18, 19], and the relationship between emotions and contextual factors such as peer interactions [7] in a typical everyday environment. The use of youth’s smartphones as a data collection tool allows for more ecologically valid sampling that avoids problems related to retrospective reporting [20] and makes participation more accessible to youth who live in rural and remote areas. This approach harnesses a technology that is already readily used by youth; Statistics Canada reported that in 2018, 97.9% of Internet users aged 15–24 years had a smartphone, and 57.5% checked their smartphone at least every 30 min [21].

The use of EMA also allows for data collection unconstrained by the original constructs of established questionnaires (i.e., anxiety questionnaires will assess the perception of anxiety in one specific timeframe/context). This data offers a unique opportunity to examine temporal relationships between symptoms and experiences that have not been previously investigated in youth with chronic pain. Importantly, while the literature on the use of EMA in pain research is well-established, it is generally described as a one-way data collection tool, whereby participants submit their diary ratings but are not provided any specific feedback or opportunities to interact with their data [22–24]. In cases where a data summary report is shared back with participants, this is conceptualized as more of an assessment outcome than an active intervention, whereby participants are provided a personalized profile at the end of the study but do not interact with their data throughout the data collection period [25].

We hypothesize that allowing pediatric patients to visualize personal health data in an accessible and youth-focused format will enable them to validate their perceptions around their chronic pain journey, understand how their symptoms relate to other areas of their everyday lives, and track and improve their general functioning. We propose building an interactive and personalized data visualization mobile application which will allow clinicians and patients to view EMA-collected data in ways which may aid in their treatment or pain-management process [26]. Such an approach to data collection may provide the opportunity for mutual benefit to all key user groups, namely researchers, clinicians, patients, and their families. We have focused our daily data collection on variables that are known to affect the functioning and treatment outcomes of youth with chronic pain, but where there is not compelling data for how these variables fluctuate and interact with pain on a day-to-day basis; namely, emotions, somatic symptoms, social experience, and sleep [15, 27–30].

Applying digital health approaches to the treatment of chronic pain is not new. A 2015 study identified nearly 300 pain self-management apps, but found they were overly simplistic, lacked involvement of health professionals or theoretical basis, and had not been rigorously tested for effectiveness [31]. The present approach is based on the Common Sense Model of Self-Regulation by Leventhal and colleagues [32], where youth act as “common-sense scientists” by populating and reflecting on informative representations of their symptoms, generating goals for self-management, and receiving feedback. This approach is consistent with evidence-based strategies for pain management (i.e., CBT, cognitive behavioral therapy), whereby patients are asked to notice patterns between thoughts, feelings, and behaviours. The digital application designed for this protocol takes input from health professionals, computer science and visualization experts, young people, and other relevant stakeholders. It overcomes a major therapeutic barrier: obtaining reliable, understandably portrayed data from patients’ everyday life upon which to evaluate these patterns and set goals.

### Objectives

We will determine whether visualization of multiple dimensions of real-world self-reported measures of somatic symptoms, emotions, functioning, and social experience is usable, accessible, and understandable to youth with chronic pain. We will also collect preliminary data on the relationship between daily reported emotions and somatic symptoms, social experience (peer interaction), and functioning (sleep, school attendance) in youth with chronic pain, as assessed by EMA self-report, as well as preliminary data on whether interacting with visualized data of these interactions can be effective in supporting youth to understand and manage their pain and associated symptoms. This pilot feasibility study is intended to be the first step in conducting a larger randomized trial of data visualization as an intervention for chronic pain in the future. This project is designed to put patients at the center of a meaningful data supply-review-act-iterate process. We envision enabling participants to use their own real-world data to make decisions about how to manage their pain [33]. To our knowledge, this is the first project to harness the visualization of youth’s symptom-tracking data as the intervention itself.

### Materials

#### Design and development of personal data visualization intervention

The initial development of the visualizations was conducted as part of a graduate design course team project offered by the University of British Columbia’s *Designing For People (DFP)* graduate training program. Pilot EMA data was collected from the five graduate students working on the project, and prototype visualizations developed with input from content experts and youth. Our initial data visualization dashboard was developed with a diverse group of students and faculty, representing a variety of racial, ethnic, cultural, and language backgrounds with a common goal of making data understandable to a wide audience. The current version of the “personal data visualization dashboard” offers multiple customized approaches (using standard charts like line charts, bubble charts, bar graphs, heatmaps, as well as custom-designed visualizations) to visualizing dimensions such as sleep, emotional well-being, physical health, and social interactions based on the individuals’ own EMA data. The primary objective of the visualizations is to reveal how these dimensions are interacting with each other for this individual (e.g., how sleep influences anxiety). These visualizations have been developed in an iterative process, considering primary patient and clinician requirements. The design and prototyping of these visualizations were guided by information visualization and human-centered design experts and validated with clinician feedback. It implements user-centered design and data visualization principles, to ensure an optimal patient-centered application. Industry partners *Careteam* [34] will provide their clinically tested and broadly available platform to capture the baseline questionnaires, record daily EMA data, and present our data visualizations. Further development in collaboration with *CareTeam* and pilot-testing engaging youth with chronic pain is currently underway and will be described in a forthcoming publication. The visualizations with their patient-specific data will be embedded directly in the CareTeam web platform for real-time results and ease of use. A near-final draft of the sample visualizations (currently undergoing user testing) is available in Additional file 1.

## Methods

This protocol was prepared in accordance with the SPIRIT (Standard Protocol Items: Recommendations for Interventional Trials) 2013 guidelines for reporting protocols of clinical trials [35, 36] and the CONSORT (Consolidated Standards of Reporting Trials) extension for pilot and feasibility trials [37]. A SPIRIT checklist has been included as Additional file 2.

### Study design

We will conduct a randomized, single-center, open-label crossover trial with a 1:1 allocation ratio, exploratory framework.

### Setting

This study will be conducted out of the Complex Pain Service (CPS) at a large tertiary-care hospital in Western Canada. The CPS provides assessment, consultation, and treatment of chronic, complex, and/or persistent non-cancer pain for children and youth up to age 18. Children and youth are referred to for wide range of painful conditions where, regardless of their etiology, pain commonly significantly interferes with daily function and has persisted despite treatments implemented by the community/referring provider.

### Participants

We will aim to recruit 50 youth with complex pain from the CPS.

#### Inclusion criteria

Youth will be eligible if they are between 12 and 18 years old and have any type of chronic pain (i.e., pain that has persisted for >3 months). Youth and parents must have sufficient command of English to provide consent/assent and for the youth to complete the study tasks in English. Youths are not required to have a smartphone to participate.

#### Exclusion criteria

Youth are not eligible if they have a diagnosis of cerebral palsy, autism spectrum disorder, learning disabilities, attention-deficit-hyperactivity disorder, or a genetic/metabolic disorder that interferes with their ability to complete the tasks required for this study (i.e., self-report on their symptoms and provide feedback on their experience). Of note, our team is undergoing separate research to investigate the use of in-home data collection and visualization in youth across the developmental spectrum [38].

#### Recruitment

Potential participants will be contacted by email by a Research Coordinator (not involved in their clinical care) and invited to complete the study. Participants will be recruited from active/recent patients in the Complex Pain Service and from past participants of research studies conducted in our clinic who consented to be contacted about research opportunities^1^. Our recent research studies have had a 90.5% rate of consent to contact regarding research opportunities, and a 62% enrollment rate in research studies (with a 23% drop-out rate among those who consented to participate) in available studies from this same population [38]. If needed, we intend to use purposive sampling to recruit a sample of participants for the present project that reflects the diversity observed in the CPS.

### Procedures

Complete procedures are outlined in Fig. 1. Consent and assent for all participants will be obtained from youth and parents/caregivers. Youth will complete baseline questionnaires prior to randomization. Once participants have been assigned to groups, the smartphone-administered EMA data collection will be completed by the youth for two 7-day periods with a 7-day break in between (washout period). Participants who do not have access to a smartphone will be loaned a pre-paid, data-enabled smartphone for the duration of the study.^2^ The trial will utilize an A-B crossover design in which participants will be randomly assigned to receive either Part A (EMA alone) or Part B (EMA plus visualization) first and then receive the opposite phase after the 7-day break. In Part A, the data collection will occur through EMA (repeated self-report via smartphone). In Part B, the data visualization will appear immediately after data entry, updating as new data is added and allowing the participant to interact with their data as the visualizations change throughout the week. Youth will be oriented with basic instructions on how to navigate the visualization platform, what the visualizations represent, and how to interpret them.

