#### Secondary outcomes

Relationships between daily measured variables will be assessed by examining the data collected through the EMA, as described above. This data will also be examined to determine preliminary differences between Part A and Part B.

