#### Secondary outcomes

Multi-level modeling will be employed to account for the nested nature of the data and accommodate any missing data, examining patterns of association between variables (both concurrent and time-lagged) at the within- and between-participant level. Previous reports have indicated that a sample size of 50 is sufficient to conduct such analyses [13]. Specifically, we will examine whether stressful events (e.g., negatively perceived peer interactions) and avoidance at time 1 predict somatic and pain symptoms at time 2, moderated by anxiety. Qualitative content analysis will be used to summarize common themes reported by participants regarding the effectiveness of the visualization application based on their feedback provided in the follow-up questionnaire. Data gathered through the EMA over the length of the study will also be quantitatively analyzed to check for clinical improvement following Part A and Part B.

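### The 7-day washout may not clear an intervention that works through learning; if benefit persists, the preliminary Part A versus Part B symptom contrast is attenuated

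*Protocol article*

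**What the plan says.** The design is fixed under Study design: "We will conduct a randomized, single-center, open-label crossover trial with a 1:1 allocation ratio, exploratory framework". Under Procedures, EMA is completed in "two 7-day periods with a 7-day break in between (washout period"), and participants "receive either Part A (EMA alone) or Part B (EMA plus visualization) first and then receive the opposite phase after the 7-day break". No reason is given why 7 days is enough.

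The mechanism of Part B is stated several times. The Abstract proposes that "interacting with self-reported data will impact the experience of pain by altering understanding and expectations of symptom experience". Background and rationale hypothesizes that seeing their data will let youth "understand how their symptoms relate to other areas of their everyday lives, and track and improve their general functioning". The same section cites a self-regulation model in which youth reflect on their symptoms and set self-management goals, and Objectives envisages participants using their data to decide how to manage pain. Procedures adds: "Youth will be oriented with basic instructions on how to navigate the visualization platform, what the visualizations represent, and how to interpret them". In the B-first sequence all of this comes before Part A.

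Three comparisons depend on the break:
- Outcomes, Secondary outcomes: "This data will also be examined to determine preliminary differences between Part A and Part B".
- Data analysis, Secondary outcomes: the EMA data will be "quantitatively analyzed to check for clinical improvement following Part A and Part B".
- Data analysis, Primary outcomes: completion is compared between the two parts, with better compliance expected in Part B.

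Explanation for the choice of comparators gives the purpose: to separate the effect of self-monitoring from that of seeing the data.

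**The concern.** A crossover contrast is free of bias only if the second period carries no more residue from one condition than from the other. A break removes the dashboard, but it does not remove what a participant has learned from it. If Part B does what the protocol hopes, youth in the B-first sequence enter Part A already knowing something about their symptom patterns. Their Part A week then measures EMA plus retained insight, which is not the comparator the protocol says it needs.

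What is at stake is how the A-B difference is read. Preliminary evidence of effectiveness is one of the Objectives, and the pilot is described as the first step toward a larger randomized trial. A real effect could appear small or absent because it lasted.

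**Working it through.** **The plan's own figure.** Power calculation gives a 95% CI of 69–91% for 80% retention with 50 participants. Check: 0.80 ± 1.96 × √(0.8 × 0.2 / 50) = 0.80 ± 0.111, or 68.9% to 91.1%. It reproduces, and it does not depend on the washout.

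**Expected crossover estimate.** Let τ be the direct effect of B over A, d the period effect, and c_A and c_B the carryover of each part into the second period.
- A-first: E(B − A) = τ + d + c_A
- B-first: E(B − A) = τ − d − c_B
- Average of the two, which removes d: τ + (c_A − c_B)/2

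Both parts include EMA, so only the excess carryover specific to visualization matters. Write that excess as c_B − c_A = sτ. The expectation becomes τ(1 − s/2).

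The documents give no value for s, so it is an assumed range:

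| Share persisting, s | Expected estimate as a share of τ |
|---|---|
| 0 | 100% |
| 0.25 | 87.5% |
| 0.5 | 75% |
| 0.75 | 62.5% |
| 1 | 50% |

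A simulation (10,000 runs, 50 participants, assumed τ = 0.5 SD, within-person correlation 0.5) gave 99%, 75% and 50% at s = 0, 0.5 and 1. The first-period comparison recovered 99–100% of τ throughout.

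**Completion.** The expected motive for better compliance is that entries populate the visualization, and that motive ends with Part B. Losing the dashboard could lower compliance in a later Part A, so s could be negative. At s = −0.5 the estimate is 125% of τ, away from zero.

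**Precision, in SD units.**
- First period, 25 per group, unadjusted: √(2/25) = 0.283.
- Crossover, with the 23% drop-out quoted under Recruitment: 50 × 0.77 = 38.5, so 38 completers. SE = √(2(1 − ρ)/38), which is 0.162 at ρ = 0.5 and 0.126 at ρ = 0.7 (assumed correlations).

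**Bias against variance**, at an assumed τ = 0.5 SD and ρ = 0.5:
- s = 0.5: bias 0.125, root mean squared error √(0.162² + 0.125²) = 0.20.
- s = 1: bias 0.25, root mean squared error √(0.162² + 0.25²) = 0.30.
- First period only: no bias, 0.28 at every s.

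**The case against.** The strongest reply is that little in this pilot rests on the contrast. It is secondary, and the article calls it preliminary and exploratory. The primary outcomes are recruitment, retention, completion, acceptability and engagement. This stands, and it limits the weight of the point.

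Three stronger readings are tempting, and the documents do not support them.

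- **A reader might infer that the larger trial will be oversized.** If the attenuated effect were used for planning, the required size would grow by 1/0.75² = 1.8 or 1/0.5² = 4. But Power calculation takes only a standard deviation and a retention estimate from the pilot, and the Abstract rests the decision to proceed on feasibility and acceptability. A constant carryover shifts a mean and leaves the SD alone. No stated use produces these multiples.
- **A reader might infer that the contrast is biased toward zero as a matter of fact.** The bias requires that Part B works and that its excess benefit outlasts the break. The protocol never says that the effect is durable; that is an inference from the mechanism.
- **A reader might see a contradiction in looking for improvement following Part B,** since EMA after Part B exists only in the B-first group's Part A week. That rests on one loosely used word, which may simply mean after exposure to each part. Nor does the absence of EMA before the first period invalidate a randomized contrast.

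It is also fair to say that the first-period comparison is no better as a sole estimate. At half persistence the crossover is the more accurate (0.20 against 0.28), and at full persistence the two are about equal.

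Model terms may be left to an analysis plan that is not shown. That does not dispose of the point: the washout and sequences are fixed here, and with two sequences and two periods a carryover difference cannot be separated from a difference between the sequence groups. A carryover test with 50 participants would have low power.

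**Conclusion.** The point holds in conditional form. The protocol relies on a 7-day washout while describing a mechanism that a break would not be expected to reverse. If Part B works and visualization-specific benefit persists, the pooled symptom contrast is attenuated by half of that carryover, to between 100% and 50% of the true effect as the persisting share runs from 0 to 1. The share is assumed and cannot be derived from the documents. For EMA completion the bias could run either way. The primary feasibility outcomes other than the A-B completion comparison, and the sample size justification, are unaffected. What changes is the meaning of a small or null A-B difference.

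**What to change.** For the preliminary symptom and completion contrasts:

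1. Report the randomized first-period comparison (B-first versus A-first over their first 7 days), with symptom outcomes adjusted for the baseline PROMIS scores already collected.
2. Beside it, report the crossover contrast from a model with condition, period and a participant random effect, and show results by sequence.
3. Present the B-first group's Part A week as a description of persistence, not as a clean control.
4. State that a small or null pooled symptom contrast cannot be read as lack of effect and should not alone supply an effect size for the larger trial.
5. State that dashboard access is limited to Part B. The article implies this but does not say it.

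The cost is analysis and reporting text plus a statement on platform access, with no extra participants or visits. The downside is the wider first-period interval: about ±1.96 × 0.283 = ±0.55 SD before baseline adjustment. That is why it is reported beside the crossover estimate and does not replace it.
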